#### Measures/outcomes

Table 2 provides an overview of the assessments used.

**Table 2 Tab2:** Overview of the assesments used

Instruments	Domains covered	Items
*Psychological assessment*		
Regensburg COVID documentation (ReCoRD)	Primary COVID-19 symptoms, current post-COVID symptoms (25 frequently reported complaints of different organ systems); relevant medical history	25
Work ability index (WAI) Ilmarinen [14]	Demands of the job, health status, resources of the worker	7
Personal health questionnaire (PHQ) Spitzer et al. [15]	Depressive, anxiety,somatoform disorders, psychosocial functionality, stressors, critical life events	78
Dissability assessment (WHO-DAS 2.0) Üstün et al. [16]	Cognition (understanding & communicating), Mobility (moving & getting around), Self-care (hygiene, dressing, eating & staying alone), Getting along (interacting with other people), Life activities (domestic responsibilities, leisure, work & school) and Participation (joining in community activities)	36
Life skills (LK-18). Hinterberger, Walter and Galuska [17]	Well-being, self-regulation, commitment, sense of purpose, self-efficacy and social contacts	18
Fatigue scale for motor functioning and cognition (FSMC) Penner et al. [18]	Subjectively experienced fatigue symptoms, graduation of cognitive and motor fatigue	20
Avoidance-endurance questionnaire (AEQ). Hasenbring et al. [19] (alternatively: Avoidance-Endurance Questionnaire, short Version (AE-FS).)	Fear-avoidance responses and endurance-related responses (cheerful-suppressive way and a distress-endurance way)	49
*Neurological assessment*		
Montreal cognitive assessment (MoCA). Nasreddine et al. [20]	Various cognitive abilities such as memory, language, contextual thinking, attention and concentration, behaviour, arithmetic, temporal and spatial orientation and the ability to recognise complex shapes and patterns	30
Test battery for attention (TAP) Scherwath et al. [21]	Intensity of attention, Executive functions, control of the focus of attention, Attentional selectivity, focused attention, visuo-spatial attention	45 min
*Somatic assessment*		
Six-Minute walk test (6MWT) Enright [22]	Assess and control cardiovascular and pulmonary performance below the anaerobic threshold	
Spiroergometry Kroidl et al. [23]	Function of the heart, circulation, respiration and muscle metabolism in a relaxed state and under increasing physical stress up to maximum load	
Pulmonary function test [24, 25]	Functional and performance capacity of the lungs and bronchial tubes; monitoring the course and therapeutic success of lung diseases	
Blood gas analysis and laboratory (blood test) Haber [26], Boemke et al. [27]	Blood test that measures how much carbon dioxide and oxygen are in the blood; conclusions can be drawn about the health of the heart and lungs	
Caridac echo Picard and Weiner [28] Carmeli et al. [29]	Information about the structure of the heart (e.g. size of the heart chambers, function of the heart valves, thickness of the heart muscle)	
24-h ECG Mehraeen et al. [30], Ståhlberg et al. [31]	Information about how the heart functions under everyday conditions	
*Post-exercise malaise/adverse events monitoring*		
Structured recording of adverse event/fatigue	Fatigue level, post-exercise malaise / adverse events	

#### Psychological assessment

##### The Regensburg COVID documentation (ReCoRD)

The ReCoRD is a self-report questionnaire and is used for the structured and quantitative assessment of the primary COVID-19 symptoms, the current post-COVID symptoms and the relevant medical history. A total of 25 frequently reported complaints of different organ systems in the context of post-COVID are recorded (e.g. cough, shortness of breath, palpitations, headaches, concentration disorders, depression, sleep disturbance, odour/taste disorders, neuropathy). The presence is recorded dichotomously. Furthermore, it is asked to what extent the symptoms were already present before, how long they have existed since the COVID-19 illness, as well as the frequency and current intensity of the complaints.

##### Work ability index (WAI)

The WAI is a well-established instrument used in clinical occupational medicine and research to assess work ability during health examinations and workplace surveys. The index is determined based on the answers to a series of questions assigned to the seven WAI dimensions, which take into account the demands of the job, the health status and the resources of the worker (Current work ability compared with the lifetime best; Work ability in relation to the demands of the job; Number of current diseases diagnosed by a physician; Estimated work impairment due to diseases; Sick leave during the past year (12 months); Own prognosis of work ability two years from now; Mental resources) [14]. The WAI has sufficient psychometric properties [14, 32, 33].

##### Personal health questionnaire (PHQ)

The PHQ is an internationally established questionnaire screening for the systematic assessment of mental disorders. The complete version consists of a total of 78 items, which are divided into 16 sections. The items are assigned to different response categories (dichtotome yes–no questions; three- to four-level ordinal scales). The structure of the PHQ is modular and thus enables targeted screening of depressive, anxiety or somatoform disorders, as well as eating disorders and alcohol abuse. In addition, questions on psychosocial functionality, stressors, critical life events and a gynaecological history (menstruation, pregnancy, birth) can be recorded, as well as global functional limitations due to psychological symptoms [15]. In this study, all modules except eating disorders, alcohol abuse and the gynaecological history are used.

##### Disability assessment (WHO-DAS 2.0)

The WHODAS 2.0 is a self-assessment instrument for health and disability, which can be used across all diseases, including mental, neurological and addictive disorders. The instrument covers six domains of functioning, including Cognition (understanding & communicating), Mobility (moving & getting around), Self-care (hygiene, dressing, eating & staying alone), Getting along (interacting with other people), Life activities (domestic responsibilities, leisure, work & school) and Participation (joining in community activities). The domains are directly linked at the level of the concepts to the International Classification of Functioning, Disability and Health (ICF). In this study we use the more detailed 36-item version, which can be self-administered in paper–pencil format. The items are assigned to a five-level ordinal scale (none–0, mild–1, moderate–2, severe–3, extreme–4); the summary score indicates the extent of impairment [16, 34].

##### Life skills (LK-18)

The life skills questionnaire LK-18 is a self-assessment instrument developed on the basis of psychosomatic inpatients, which covers the areas of well-being, self-regulation, commitment, sense of purpose, self-efficacy and social contacts by means of 18 items, which can be divided into 6 factors with 3 items each. The items are rated on a 5-point scale. The recorded life skills represent abilities from which a salutogenic lifestyle can result, which in turn can serve as a basis and important indicator for the therapeutic process [17].

##### Fatigue scale for motor functioning and cognition (FSMC)

The FSMC is an assessment which grasps subjectively experienced fatigue symptoms and which provides differential quantification and graduation of cognitive and motor fatigue. The FSMC was tested against several external criteria (e.g. cognition, motivation, personality and other fatigue scales) and provides satisfactory results with regard to the test quality criteria. Twenty items (10 for motor fatigue, 10 for cognitive fatigue) are rated using a five-point scale (strongly disagree to strongly agree) [18].

##### Avoidance-endurance questionnaire (AEQ)

The Avoidance-Endurance Questionnaire [19] uses 49 items to assess behaviours that may contribute to chronicity of symptoms. A distinction can be made between two processing modes: fear-avoidance responses and endurance-related responses (cheerful-suppressive way and a distress-endurance way). The cheerful-suppressive way involves focused forms of cognitive distraction from symptoms, maintaining a positive mood despite suffering, and continuing daily activities even in the presence of intense distress (eustress-endurance responses). The other way (distress-endurance responses) is characterised by unspecific suppression of symptoms and thoughts about the symptoms, heightened irritable and depressed mood, but still strong endurance during and despite the experience of not only mild but also severe distress. The scales referring to fear avoidance responses are anxiety/depression, catastrophizing, help-/hopelessness, avoidance of social activities, avoidance of physical activities. The scales referring to endurance-related responses comprise positive mood, thought suppression, pain persistence behavior and humor/distraction. Items are rated on a seven-point scale (never to always). The AE-FS [35] is a fast screening based on the AEQ and contains 9 items. Both instruments have satisfactory psychometric properties.

#### Neurological assessment

##### Montreal cognitive assessment (MoCA)

The MoCa test is performed by healthcare professionals to detect early stages of dementia and mild cognitive impairment and to distinguish them from “normal” senile forgetfulness. The MoCa test is significantly more accurate in detecting mild forms of dementia with only slightly impaired abilities than other well-established procedures such as the MMST, which is often used in dementia diagnostics. The test, which lasts about 10 min, contains 30 questions that test various cognitive abilities such as memory, language, contextual thinking, attention and concentration, behaviour, arithmetic, temporal and spatial orientation and the ability to recognise complex shapes and patterns. Scores of 26 to 30 points are considered unremarkable, no limitations, 6 to 25 points indicate at least mild cognitive impairment, and 0 to 5 points are interpreted as extreme mental impairment [20].

##### TAP-test

The Test Battery for Attention (TAP) is a software package and offers a collection of different test procedures with which the various sub-aspects of attention can be recorded in a differentiated manner and also cover related aspects of visual perception. Subtests are Alertness, working memory, sustained attention, flexibility, divided attention and go/nogo paradigm. The test takes about 45 min to complete [21] (Table 3).

**Table 3 Tab3:** Overview of the TAP subtests used

Subtest	Cognitive domain	Information about
Alertness	Intensity of attention	Basal reactivity, general processing speed, reaction stability, distinction tonic and phasic alertness
Working memory	Executive functions, control of the focus of attention	Ability to continuously update the content of working memory
Sustained attention	Intensity of attention	Longer-term maintenance of attention with high target stimulus density
Divided attention	Attentional selectivity, focused attention, visuo-spatial attention	Ability to focus attention on two tasks simultaneously
Alertness	Intensity of attention	See above

#### Somatic assessment

##### Six-minute walk test (6MWT)

The 6MWT is used to assess and control cardiovascular and pulmonary performance below the anaerobic threshold. In the test, the patient has to walk for 6 minutes over an incline-free circuit or a walkway of at least 30 meters in length. The goal for the patient is to cover as much distance as possible in the given time window. The distance is measured in metres [22]. In addition, just before the start of the 6MWT in a standing position and at the end of the 6 minutes, respiratory distress is determined using the Borg CR10 scale [36].

##### Spiroergometry

The spiroergometric examination assesses the function of the heart, circulation, respiration and muscle metabolism in a relaxed state and under increasing physical stress up to maximum load. By simultaneously measuring the oxygen and carbon dioxide concentration in the inhaled and exhaled air, oxygen consumption (VO2) and carbon dioxide production (VCO2) can be determined [23].

##### Pulmonary function test

The pulmonary function test assesses the functional and performance capacity of the lungs and bronchial tubes. It can be used for monitoring the course and therapeutic success of lung diseases [25] and other respiratory tracts [37].

##### Blood gas analysis and laboratory (blood test)

Blood gas analysis can be used to measure how much carbon dioxide and oxygen is in the blood, and conclusions can be drawn about the health of the heart and lungs. The blood count gives an overview of the cellular components contained in the blood and allows an assessment of whether diseases are present that are initially asymptomatic [26, 27].

##### Cardiac echography and 24-h ECG

Echocardiography is one of the most important routine heart examinations. The ultrasound examination provides information about the structure of the heart and makes it possible, for example, to assess the size of the heart chambers, the function of the heart valves or the thickness of the heart muscle [28, 29]. The 24-h ECG records the electrical heart actions over mostly 24-h and thus enables the diagnosis of recurrent disorders, especially cardiac arrhythmias [30, 31].

#### Post-exercise malaise/adverse events monitoring

##### Structured recording of adverse events/fatigue

In the psychotherapy group, the fatigue level and adverse events that result in post-exercise malaise are recorded and logged in a structured manner with the addition of behavioural analysis.

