This prospective, explorative, multicentre, mixed-methods study with clinical, standardised examination will include somatic and psychological testing at three measurement points: Admission (t0), discharge (t1), 6-month catamnesis (t2). The study is going to take place in Cardiological rehabilitation, Pneumological rehabilitation, neurological rehabilitation and Psychosomatic rehabilitation. This study is in line with the Stanford Hall consensus statement for post-COVID-19 rehabilitation [12]. In a structured and quantitative way the primary COVID-19, the current post-COVID symptomatology as well as the relevant history on quality of life and functionality will be recorded. Psychological stress, e.g. in the form of depression or anxiety, is assessed via questionnaires, and the cognitive performance parameters relevant to occupational medicine are assessed via an objective neuropsychological test battery. Fatigue and other somatic aspects of physical performance and the muscular/pneumological situation are recorded in the course of medical examinations. We outline that our study protocol is in line with the research agenda of post-COVID fatigue [13]. Furthermore, this study addresses the phenomenon of post-exercise malaise, which is postulated in the line to the post-COVID syndrome, but for which there is a lack of reliable data on whether or how often this phenomenon actually occurs. Apart from that, a training-focused approach is also recommended in this context. In the context of this study, we are therefore not only testing whether rehabilitation is effective, but also whether it is safe for patients with post-COVID syndrome.

The first objective is the description of neurological, cognitive or/and psychological functional impairments in rehabilitation patients after COVID-19 disease.

The second objective is the differentiated review of the specific rehabilitation measures, in the short term and in the longer term (6-month catamnesis) for the purpose of future prognoses and optimisation of therapeutic interventions / the therapeutic offer.

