### Other research questions

3.1 To what extent does the different symptomatology (pneumological, neurological, psychosomatic) correlate with an unfavourable socio-medical evaluation.3.2 Is the type of illness behaviour (avoidance-endurance) a predictor of symptomatology and socio-medical performance assessment?3.2 Is there evidence of post-exercise malaise or other adverse events? Are there patients who deteriorate in the course of rehabilitation? (especially in the Six-Minute Walk Test)3.4.1 Are there medical parameters that can be identified as risk parameters for a unfavourable socio-medical prognosis and a prolonged course of the condition (e.g. spiroergometry, lactate test)?

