Psychosomatic rehabilitation	1 × per rehabilitation/60 min *Post-COVID and Naturotherapy* 2 × per rehabilitation/60 min *Naturotherapy for stress at work* 1 × per rehabilitation/60 min *Introduction cognitive training* 1 × per rehabilitation/30 min *Introduction cognitive training Freshminder*	1 × per week/45 min monitored strenght training 1 × per week/45 min monitored coordination training or 1 × per week/30 min aqua fitness 1 × per week/60 min Walking	1 × per week/45 min QiGong or Yoga 1 × per week/45 min meditative moving	2 × per week/ 75 min 1 × per week/ 60 min	1 × per week/30 min	2 × per week/30 min Group 2 × per rehabilitation/ 30 min single session	2 × per week/30 min Group	1 × per week/45 min meditative dancing or 1 × per week/45 min meditative forest bathing 1 × per week/30 min dew stepping Ergotherapy (as needed)	Nutrition advice (as needed) Social service (as needed) 1 × per week/ 30 min Mindfulness group Aroma therapy (as needed)
*Schmieder Clinics*									
Neurological rehabilitation *Note.* Patients have approx. 19–21 therapy sessions per week in an individual therapy plan	1 × per rehabilitation *Post-COVID* Multiple times per rehab, different topics like *smoking cessation, dietetics, overweight, muscular deficits*	After performance level assessment: Stamina training Strength training Vibration platform training	As needed (PMR)	As needed	As needed	Breathing therapy group Guided self-exercise training with breathing therapy device Oxygen therapy (as needed)	Assessment and training as needed	Daily life training (as needed) motor-functional training (as needed)	Olfactory training (as needed) Nutrition advice (as needed) Social service (as needed)
*Clinic Westerwald*									
Neurological rehabilitation *Note.* Patients have a very individual therapy plan	1 × per rehabilitation *Post-COVID* Multiple times per rehab, different topics like *fatigue, headache, dietetics,* *Smoking cessation*	After performance level assessment: stamina training strength training Vibration platform training	As needed (PMR, autogenic training)	none	1 × per week/ 60 min (as needed)	As needed	Assessment and training (CogniPlus) as needed	Compensatory and memory strategies (as needed)	Olfactory training (as needed), including Kaiteki maneuver with local application of vitamin A Speech therapy (as needed) Social service (as needed

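### Post-exercise malaise and adverse events are logged in a psychotherapy group that not every setting runs, so the log cannot give an unbiased frequency for the whole cohort or across settings

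*Protocol article*

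**What the plan says.** The Background sets a safety aim for the study as a whole: it is "not only testing whether rehabilitation is effective, but also whether it is safe for patients with post-COVID syndrome". It motivates this by saying that, for post-exercise malaise, "there is a lack of reliable data on whether or how often this phenomenon actually occurs". Under Other research questions, the second item numbered 3.2 asks "Is there evidence of post-exercise malaise or other adverse events" and continues "Are there patients who deteriorate in the course of rehabilitation? (especially in the Six-Minute Walk Test".

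The section Structured recording of adverse events/fatigue describes the recording method in a single sentence, which begins: "In the psychotherapy group, the fatigue level and adverse events that result in post-exercise malaise are recorded and logged in a structured manner". Table 2 lists the same recording as a study assessment, with fatigue level, malaise and adverse events as its domains. It names no therapy group and gives no other route.

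Table 1 has a column for group psychotherapy. In the last neurological row (the one noting "Patients have a very individual therapy plan"), the relaxation cell and then the group cell read "As needed (PMR, autogenic training) none". In the other neurological row, the relaxation, group and single-session cells read "As needed (PMR) As needed As needed". The Control group section says that the outpatient controls receive no intervention.

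**The concern.** A frequency needs a known denominator and the same chance of being recorded for everyone in it. Here the chance of being recorded is tied to attending one therapy, which the settings provide very unequally. Where the group is offered as needed, attendance also selects patients, probably on psychological burden.

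Two errors could follow. Differences in logged events between settings could reflect how often the group meets rather than how patients tolerate exercise. And a low or zero count in a clinic that does run stamina and strength training could be read as reassurance when nobody was asked. The article's Conclusion counts detection of possible adverse events among the results that would make the study relevant, so this reading is a practical risk. Events missed during a stay cannot be reliably reconstructed later, and no analysis can repair them.

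A second, smaller point lies in the same sentence. As worded, the log covers adverse events that lead to malaise, whereas the research question also asks about other adverse events.

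**Working it through.** The document gives no event rate or sample-size figure for this point, so there is no stated figure to reproduce. The check sets the recording rule beside the Table 1 column for group psychotherapy.

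| Programme in Table 1 | Group psychotherapy |
|---|---|
| Pneumological department (first clinic) | 2 per stay |
| Psychosomatic department (first clinic) | 2 + 1 = 3 per week |
| Psycho-pneumological department (first clinic) | 3 per week |
| Pneumological clinic (second clinic) | 1 per week, as needed |
| Psycho-cardiological clinic | 2 per week |
| Psychosomatic clinic | 2 + 1 = 3 per week |
| Neurological provider | as needed, no frequency given |
| Neurological clinic (last row) | none |
| Outpatient controls (Control group section) | no intervention, hence no group |

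**Count.** Of the 8 rehabilitation programmes, 5 schedule the group, 2 offer it as needed and 1 has none. By listed clinic (6), the split is 3, 2 and 1. No neurological programme schedules it.

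**Patients concerned.** Enrolment per clinic is not given. Assuming equal enrolment of the 1000 cases:
- no scheduled group: 1000 × 3/8 = 375 by programme, or 1000 × 3/6 = 500 by clinic;
- of these, no group at all: 1000 × 1/8 = 125, or 1000 × 1/6 ≈ 167.

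**Logging does not follow exercise exposure.** Two departments of the first clinic have the same weekly exercise time. The pneumological department has 3 × 30 + 5 × 30 = 240 minutes, and the psycho-pneumological department 2 × 60 + 4 × 30 = 240 minutes. The first offers 2 logging occasions in the whole stay, the second 3 every week. The neurological clinic with no group lists stamina, strength and vibration-platform training and offers no logging occasion.

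**Illustration only.** Assume a 4-week stay and an equal, independent chance p that any one session logs an episode. Neither is in the document. The share of patients with at least one logged episode is 1 − (1 − p)^n for n sessions:

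| Sessions n | p = 5% | p = 10% |
|---|---|---|
| 0 (none) | 0% | 0% |
| 2 (2 per stay) | 10% | 19% |
| up to 4 (weekly, as needed) | up to 19% | up to 34% |
| 8 (2 per week) | 34% | 57% |
| 12 (3 per week) | 46% | 72% |

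The underlying risk is identical in every row. The spread depends on the recall period, which is not stated. If each entry covered all the time since the previous session with full recall, the gap between 2 and 12 sessions would shrink. The zero where there is no group would remain.

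**Scope of the log.** The recording section ties adverse events to those resulting in malaise. Table 2 names malaise and adverse events side by side. The research question asks about malaise or other adverse events. The first is narrower than the other two.

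**The case against.** The strongest reply is that the article never says the psychotherapy group is the sole place of recording. Table 2 lists the assessment without restriction, the study-procedure figure is not shown, and a journal article may leave adverse-event procedures to the full protocol. That is fair, and exclusivity is an inference. But the article does fix a place of recording, that place conflicts with its own Table 1, and no other route is described.

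A reader might infer that the safety question cannot be answered at all. The document does not support that. The same research question also rests on deterioration in the six-minute walk test, which does not depend on psychotherapy; breathlessness is rated at that test, and the FSMC measures fatigue. Asking whether there is evidence of malaise is a question of existence, which the groups that run can answer, and it stands among the other questions of an explorative study. This part of the objection stands. What it does not rescue is frequency: the Background raises how often malaise occurs, and change scores on a walk test or fatigue scale do not count episodes or adverse events.

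A reader might also infer that adverse events not leading to malaise are never captured. Table 2 is worded more broadly, so this is an inconsistency to resolve and not proven non-capture.

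Two further objections hold in part. The question about deterioration concerns the course of rehabilitation, so the lack of a group for controls matters only if a comparison with them is intended. And the session-based percentages show a model, not the study; the article itself says that therapy times in the neurological clinics cannot be set out in advance.

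**Conclusion.** The point holds in limited form. Followed as written, the log cannot give an unbiased frequency of malaise or adverse events for the whole cohort, and it cannot support comparison between settings, neurology above all. It offers no comparison with controls either. It can show whether malaise occurs where groups run, and the walk test and FSMC cover another part of the safety question.

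The firm part is the count from Table 1: 3 of 8 programmes, including both neurological ones, have no scheduled occasion for the log, and the scheduled ones range from 2 sessions per stay to 3 per week. The patient numbers (375 to 500 without a scheduled group) assume equal enrolment. The percentages of patients with a logged episode are illustrative and should not be quoted as expected results. The conclusion also assumes that no unrestricted route exists in a document not shown; if one does, the remedy is to state it.

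**What to change.** Detach the log from the psychotherapy group. Use one short form with a fixed recall period for every enrolled rehabilitation patient in every clinic at fixed times: at minimum at discharge (t1) with the other questionnaires, preferably weekly. Put the same questions to controls at their existing questionnaire contacts where a comparison is wanted. Record all adverse events and code post-exercise malaise as one category. Report by setting, with the number of patients assessed as denominator, so that a clinic with no assessments shows as not assessed and not as zero events.

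Reword the recording section so that it agrees with Table 1, Table 2 and the second question 3.2. If a route for patients outside the group already exists, say so there.

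The cost is a one-page form, a few minutes per patient on each occasion, some data entry and a change of wording. It changes data collection only and leaves treatment as it is.

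### The malaise and adverse event log sits in the psychotherapy group, which one neurological clinic does not have and two other clinics offer only as needed, so the log cannot carry the general safety statement

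*Protocol article*

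**What the plan says.** The Background section notes of post-exercise malaise that "there is a lack of reliable data on whether or how often this phenomenon actually occurs", and goes on: "we are therefore not only testing whether rehabilitation is effective, but also whether it is safe for patients with post-COVID syndrome". Under Other research questions, the second item numbered 3.2 asks "Is there evidence of post-exercise malaise or other adverse events", followed by a separate sentence: "Are there patients who deteriorate in the course of rehabilitation? (especially in the Six-Minute Walk Test".

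Table 2 lists one instrument for fatigue level, malaise and adverse events, with no restriction to any department. The section on structured recording of adverse events/fatigue says where it is used: "In the psychotherapy group, the fatigue level and adverse events that result in post-exercise malaise are recorded and logged in a structured manner", with a behavioural analysis added. The article describes no other structured recording of malaise or adverse events and gives no recording interval.

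Table 1 has separate psychotherapy columns for group and single sessions. For Clinic Westerwald, the relaxation, group and single-session cells read in sequence "As needed (PMR, autogenic training) none 1 × per week/ 60 min (as needed", so the group cell is the word none. For the Schmieder Clinics the same three cells read "As needed (PMR) As needed As needed". The control group section says that the outpatient setting is diagnostic only, without intervention.

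**The concern.** Safety is posed as a question about post-COVID rehabilitation patients in general, but the log is attached to a treatment that only some of them receive. Whether a patient can enter the log, and how often, is then decided by the programme or by referral to psychotherapy.

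Three things are at stake. A patient at a clinic without the group has no described route into the log. At an as-needed clinic the logged patients are those judged to need psychotherapy, who may differ from the rest in fatigue and symptom burden. Where the group is scheduled, more sessions mean more chances for an event to be reported. Analysis cannot recover events that nobody asked about, so the gap has to be closed at data collection.

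**Working it through.** No sample size, power or error-rate figure bears on this point, and the plan has no figure of its own to reproduce. The check sets the recording rule against the group psychotherapy column of Table 1.

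**Inputs from Table 1** (the Alpcura sub-rows counted as one programme):

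| Programme | Group psychotherapy | Coverage |
|---|---|---|
| Todtmoos, pneumological | 2 per stay | scheduled |
| Todtmoos, psychosomatic | 2 + 1 = 3 per week | scheduled |
| Todtmoos, psycho-pneumological | 3 per week | scheduled |
| Alpcura, pneumological | 1 per week, as needed | by referral |
| Seehof, psycho-cardiological | 2 per week | scheduled |
| Gelderland, psychosomatic | 2 + 1 = 3 per week | scheduled |
| Schmieder, neurological | as needed | by referral |
| Westerwald, neurological | none | absent |

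**Counts.** Scheduled 5, as needed 2, none 1; 5 + 2 + 1 = 8. By type:

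- neurological: 0 of 2 scheduled
- pneumological: 1 of 2 scheduled, at two sessions per stay
- psychosomatic, psycho-cardiological and psycho-pneumological: 4 of 4 scheduled

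These are counts of programmes. Enrolment by clinic is not given, so they are not shares of patients.

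**Recording occasions.** Suppose each session is one occasion to report; this is an assumption, since no recording frequency is stated. Over a stay of w weeks the scheduled programmes then offer 3w, 2w or a flat 2 occasions. The length of stay is not given. With an assumed w = 5 this is 15, 10 and 2, against 0 to 5 at Alpcura, 0 at Westerwald and an unknown number at Schmieder. For any stay longer than one week, the pneumological programme at Todtmoos has the fewest occasions of the five.

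**Direction of bias.** If all enrolled patients form the denominator, the expected logged frequency is the sum over programmes of (share of patients) × (true frequency) × (probability that an event is logged). The last factor is zero where there is no group, which pulls a pooled figure down. If only patients in the group form the denominator, referral can push the figure either way, and Westerwald contributes no data rather than a rate of zero. Enrolment shares, true frequency and logging probability are all unstated, so no magnitude follows.

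**The case against.** **Harm is also assessed elsewhere.** The research question on deterioration points to the six-minute walk test. That test with its Borg rating, the FSMC, the WHO-DAS 2.0 and the ReCoRD symptom intensities are study assessments not tied to psychotherapy. The Background also says that fatigue is recorded in medical examinations. This stands, and it limits the point to structured recording during the stay. It does not remove the point: the Study variables section places the study tests at admission and discharge, with a later follow-up. A net change between visits does not record malaise after exercise or an adverse event in between.

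**The rule does not say only.** Westerwald offers single psychotherapy sessions as needed, the study procedure figure is not shown, and a fuller protocol may describe other recording. This is fair as a caution. But the article does not leave the place of the log open. It names it, and its own table shows that place to be absent or selective in three programmes. If psychotherapy group was meant as the psychosomatic cohort, coverage is narrower still.

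**No malaise rate is announced.** The Background remark on frequency describes existing evidence, and the research question asks whether malaise exists. No pooled frequency or between-setting malaise comparison is stated. This stands, so the timetable effect is a warning about how the log may be used, not an error in an announced analysis.

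**A tempting stronger reading.** A reader might infer that harm goes unrecorded in whole indications. Table 1 does not support that: neurology has an as-needed group at Schmieder, and pneumology a scheduled one at Todtmoos.

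**It is a third-tier question in an explorative study.** True; the primary and secondary research questions are untouched. Safety is nonetheless put beside effectiveness as something the study tests.

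**Conclusion.** The point holds in a limited form. Followed as written, structured recording of malaise and adverse events during the stay is absent in one of eight programmes, dependent on referral in two, and guaranteed in neither neurological programme. In the five that schedule the group, its frequency varies from two sessions per stay to three per week. The control group has no place for the log at all. The log therefore cannot support a general statement that rehabilitation is safe, and differences in logged malaise between settings would partly mirror the timetable.

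This rests on reading the recording rule as the only structured log, which is all that the article describes. It does not show that harm as a whole goes unmeasured, nor that any clinic would report a particular rate. A numerical bias would need enrolment shares, length of stay, referral rates and a true malaise frequency, none of which the document gives.

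**What to change.** Take the log out of the psychotherapy group. Have every rehabilitation patient complete the same short form on fatigue, malaise and adverse events at one fixed calendar interval, for example weekly, handed out at an existing contact other than that group. The interval should follow the calendar and not the number of sessions of any therapy: exercise therapy appears in every programme, but both neurological clinics give no frequency for it, and the note to Table 1 says their therapy times cannot be stated in advance. Report frequencies per patient and per patient-week actually observed.

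Where this is not done, limit malaise and adverse event statements to programmes whose psychotherapy group is scheduled for all patients, and make no pooled, between-setting or controlled safety claim from the log. A form given to rehabilitation patients alone still provides no controlled comparison, and the text should say so.

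The cost is one revised protocol paragraph, a one-page form and a little documentation time. No treatment changes and no examination is added.
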